### Inclusion and exclusion criteria

#### Sample size

The study is powered at 80% (α =0.05) to detect a mean difference of 3.7 points in HIT6 before and after treatment. A pooled calculation of standard deviation (SD) of 4.91 was calculated for the Headache Impact Test (HIT6) from the analysis of major studies in chronic migraine [7, 54–59]. Although this requires 29 participants in each group, 32 will be recruited to allow for attrition that may be experienced over a 12 week period.

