**Methods:**

A pragmatic, randomised controlled trial in a hospital tertiary headache clinic**.** Participants will be randomised into one of two groups: treatment as usual or treatment as usual plus manual therapy. The primary outcome measure will be a change in the Headache Impact Test score. Secondary outcomes will also be measured over the 12-week study period including changes in headache frequency, migraine specific quality of life and reductions in relevant medicine consumption. The manual therapy group will have five treatment sessions each lasting 30 min. The recruitment target of 64 participants will allow power at 80% with *p* = 0.05 using minimal clinical difference for Headache Impact Test of 3.7 and includes provision for a 10% dropout rate. Recruitment will take place between August 2018 and February 2019. The results will form part of a doctoral study and be published in peer-reviewed journals and presented at national/international conferences.

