#### Outcome measures

The primary and secondary endpoints are differences in within-group changes between groups in the outcomes listed below (Table 5). These will be measured using the weekly diaries and the validated instruments in the baseline and 12-week follow-up questionnaires.

**Table 5 Tab5:** Outcome Measures

Primary Outcomes	Measurement Instrument (validity)
Migraine-related disability	Headache Impact Test (HIT 6) [54]
Secondary Outcomes	Measurement Instrument
Quality of Life	Migraine Specific Quality of Life Questionnaire (MSQ. V2.1)[59]
Use of abortive migraine medications	1.1.11.1.11.1.1Diary [69]
Percentage of participants with reduction in headache frequency (days per month) of greater than 50%	
Number of headache free days	
Stress	
Stress	Perceived Stress Questionnaire (PSS) [80]
Stress	Brief Cope [81]
Anxiety	State and Trait Anxiety Inventory (STAI-6) [63]
Anxiety & Depression	Hospital Anxiety and Depression Scale (HADS) [82]
Cutaneous Allodynia	Allodynia Symptom Checklist (ASC) [83]
Cutaneous Allodynia	Algometry [49, 84]
Patient Reported Outcome Measure	Patient Global Impression of Change Scale (PGICS) [85]

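### The power statement words its 3.7-point HIT-6 target as a before-and-after difference, while the endpoint and test are between-group; with the kind of SD unstated, 80% power is not established, though no shortfall is shown.

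*Protocol article*

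**What the plan says.** The Sample size section sets 80% power at an alpha of 0.05 "to detect a mean difference of 3.7 points in HIT6 before and after treatment". It takes its SD from published chronic migraine studies: "A pooled calculation of standard deviation (SD) of 4.91 was calculated for the Headache Impact Test (HIT6"). It concludes: "Although this requires 29 participants in each group, 32 will be recruited to allow for attrition". The Methods paragraph of the abstract describes the same figure differently, "using minimal clinical difference for Headache Impact Test of 3.7", without saying whether the difference is between or within groups.

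The Outcome measures section defines the endpoint: "The primary and secondary endpoints are differences in within-group changes between groups". The Statistical analysis section plans a Student's t test or Mann-Whitney test between groups over the 12 weeks, and the Study design section gives the objective as the difference between the two arms. No section gives a change SD, a correlation between baseline and week 12, or the sidedness of the test.

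**The concern.** Two things do not line up.

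First, the powered effect as worded is a fall within patients, whereas the trial tests a difference between arms in that fall. These are different hypotheses and need different numbers of patients. The trial has no sham arm, and the Methodological considerations section cites placebo levels of 20 to 49% in chronic migraine botox studies. A 3.7-point fall within one arm would therefore say little about manual therapy.

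Second, the planned test is on change, so the SD that governs its power is the SD of change. The article attaches 4.91 to HIT-6 without saying whether it describes scores at one visit or changes between visits. The two can differ in either direction, so the 80% claim cannot be confirmed for the planned test from what is written.

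**Working it through.** **Inputs.** Difference 3.7, SD 4.91, power 80%, alpha 0.05, 29 per group and 1:1 allocation, all from the Sample size section (the total of 64 is in Study design). Two-sided testing is inferred: a one-sided two-sample t calculation gives 22.5, so 23 per group, not 29.

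**1. Reproduce the plan's figure.** Standardised difference d = 3.7 / 4.91 = 0.754. A two-sided two-sample t test with 80% power needs n = 28.64, so 29 per group. This matches the article. Power at 29 per group is 80.5%.

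**2. Try the contrast as worded.** A two-sided paired t test with the same effect and SD needs n = 15.85, so 16 patients in all. The article's 29 per group is therefore a between-group calculation.

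**3. Find the change SD that 29 per group can tolerate.** Solving the two-sample t power for 80% at 29 per group gives a change SD of at most about 4.94.

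**4. If 4.91 is already a change SD.** Power is 80.5%, as in step 1.

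**5. If 4.91 is a score SD (assumption).** With equal SDs at both visits and correlation r between them:

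- t test on change: SD = 4.91 × √(2(1 − r))
- ANCOVA on the week-12 score, adjusted for baseline: SD = 4.91 × √(1 − r²)

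The documents give no r, so the range is shown on both sides of 0.5. Power is at 29 per group.

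| r | Change SD | Power, t test on change | n per group for 80%, t test on change | ANCOVA SD | Power, ANCOVA |
|---|---|---|---|---|---|
| 0.2 | 6.21 | 61% | 46 | 4.81 | 82% |
| 0.3 | 5.81 | 66% | 40 | 4.68 | 84% |
| 0.4 | 5.38 | 73% | 35 | 4.50 | 87% |
| 0.5 | 4.91 | 80.5% | 29 | 4.25 | 90% |
| 0.6 | 4.39 | 88% | 24 | 3.93 | 94% |
| 0.7 | 3.80 | 95% | 18 | 3.51 | 98% |

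At r = 0.5 the factor √(2(1 − r)) equals 1, so change SD and score SD coincide. Below that the t test on change loses power; above it, it gains.

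The ANCOVA SD can never exceed 4.91, because √(1 − r²) is at most 1. By this formula its power never falls below 80.5%. Allowing for the estimation of the baseline slope costs less than one percentage point, which leaves 79.8% in the extreme case r = 0.

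**6. ANCOVA if 4.91 is a change SD.** The score SD is then 4.91 / √(2(1 − r)), and the ANCOVA SD is 4.91 × √((1 + r)/2). This is below 4.91 for any r under 1, so adjustment does not reduce power in this case either (about 90% at r = 0.5 and 86% at r = 0.7).

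**The case against.** The best defence is that the disputed phrase is shorthand for a difference in before-to-after change. The same section sizes each group, the figure of 29 is exactly the two-sample result, and the objective, endpoint and test are all between-group. This stands as far as the calculation goes: the arithmetic is right for the trial. It does not rescue the sentence, because no section actually states that the trial is powered for 3.7 points between groups, and the abstract leaves that open.

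A second defence is that a condensed article may leave the type of SD and the assumed correlation to the full protocol. That has force, and the missing label alone would be a small matter. The contradiction in wording, however, is in text that the article does state, and a label belongs in the same sentence once it is rewritten.

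Three stronger readings are tempting, and the documents support none of them.

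- A reader might infer that a score SD was wrongly used in place of a change SD. Some of the pooled sources are cited elsewhere in the article for the HIT-6 instrument, for migraine disability or for the MSQ, which hints at single-visit SDs. Others are cited nowhere else, and how a source is cited does not show which SD was taken from it.
- A reader might infer that the trial is underpowered. That needs both a score SD and r below about 0.5; with r above 0.5, power exceeds the stated figure.
- A reader might infer that success will be judged on a 3.7-point fall within the manual therapy arm. No section offers that as a criterion.

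**Conclusion.** The concern holds as a defect of wording and specification. The target in the Sample size section contradicts the between-group endpoint and test, and the article's own 29 per group shows that the wording, not the number, is at fault (28.64 per group against 16 in all).

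Because the kind of SD is not stated, 80% power for the planned t test on change is not established. It is 80.5% if 4.91 is a change SD. If 4.91 is a score SD, it runs from 61% at r = 0.2 to 95% at r = 0.7 and crosses 80% at about r = 0.5. These conditional figures assume equal SDs at the two visits, a two-sided test and 29 evaluable patients per group. They show what is unsettled, not a proven loss of power.

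**What to change.** - Rewrite the target in the Sample size section as 80% power, at a two-sided alpha of 0.05, to detect a 3.7-point between-group difference in mean HIT-6 change from baseline to 12 weeks. Use the same wording in the abstract.
- Say whether 4.91 is an SD of scores or of changes.
- Make the primary analysis an ANCOVA of the 12-week HIT-6 score with baseline HIT-6 as covariate. The between-group difference keeps its meaning, and the baseline score is already collected. At 29 per group this gives 80% or more at any r if 4.91 is a score SD (82% at r = 0.2, 90% at r = 0.5), apart from the fraction of a point noted for r near 0.
- If the unadjusted test on change is kept, state its power over the full range of r, both below and above 0.5.

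The cost is a change of text and of the primary model. No extra patients, visits or measurements are needed. If the unadjusted test is kept and 4.91 proves to be a score SD, the stated power may become less favourable or more so, depending on r.

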#### Allocation

A randomisation assignment sequence will be created by an independent member of the research team using randomisation software “Research Randomizer” [60]. The results will be put into sealed opaque envelopes which the participants will open in their meeting with the PI, who will explain the process to be followed depending on the group allocation.

Immediately following the initial screening by the neurologist/specialist nurse, those participants who meet the inclusion criteria will be invited to an assessment with the Principal Investigator (PI). If this is not possible, it will be arranged within 5 days. The PI will provide participants with verbal and written information about the project before gaining written consent. He will also explain the risks, and benefits as well as the potential adverse reactions to MT and how to manage them. Potential adverse reactions may include temporary local tenderness, aching and tiredness [61]. Participants will be randomised into two groups (care as usual and care as usual plus MT).

The neurologist will be blinded as to the participant’s group allocation in order to reduce initial selection and potential contact bias. The PI cannot be blind to the manual therapy group but will be blinded to the end of study survey analysis, with an independent member of the research team detailed to recode the participant reference numbers and store the key file on a password protected computer. The unblinding of single cases by the PI/CI in the course of a clinical trial will only be performed if necessary for the safety of the trial subject.

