#### Intervention

The neurologist will manage the care as usual group alone. The care as usual and MT group will be managed by the neurologist and receive MT from the PI. The MT administered will consist solely of mobilisation, manipulation and soft tissue work. The PI will use a pragmatic approach to the MT administered, using any of the above manual interventions deemed clinically appropriate at each appointment based on assessment prior to treatment and participant feedback. The PI is an experienced chiropractor with over ten years’ clinical experience of chiropractic and soft tissue work, with postgraduate education and training in the management of CM. The treatment delivered will be recorded in the Case Report File (CRF). Failure to attend all manual therapy sessions will result in withdrawal from the study although provision will be made to provide an alternative appointment if the participant cannot make one as planned. Any change in a participant’s medical condition such that they fulfil the exclusion criteria above will result in their withdrawal from the study. Data from these participants would not be included in the final study results. Adverse events will be recorded in the CRF, and if classed as serious would be referred to the neurologist to be reported to the sponsor within 24 h of learning of the event and to the Main Regional Ethics Committee within 15 days in line with the required timeframe. The outline interventional procedure is shown in Table 3 with the project flow following the SPIRIT guidelines (Table 4).

**Table 3 Tab3:** Manual therapy protocol

1. Assess upper body^a^ posture in sitting	
2. Assess active and passive neck range of motion	
3. Assess shoulder girdle range of motion by raising each arm sideways from side of body up to ear	
4. Assess the temporomandibular joint	
5. Identify areas to treat in sitting position	
6. Administer MT using mobilisation, manipulation and soft tissue release in sitting position	
7. Assess patient shoulder girdle, neck and head supine and prone	
8. Administer MT in supine and prone position	
9. Following each session an outline of the MT used will be recorded.	
10. A total of 30 min will be allocated for each participant at these consultations	

^a^Upper body defined as from thoraco-lumbar junction upwards

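### The treating PI takes consent and attends the release of each allocation, and baseline HIT-6 may be completed once the arm is known; release should be independent of the PI and follow completed baseline

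*Protocol article*

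**What the plan says.** The protocol article describes entry to the trial mainly in its Allocation section.

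- Screening comes first and is not done by the PI: "Immediately following the initial screening by the neurologist/specialist nurse, those participants who meet the inclusion criteria will be invited to an assessment" with the PI.
- The PI then takes consent: "The PI will provide participants with verbal and written information about the project before gaining written consent". The PI also explains risks, benefits and possible reactions to manual therapy (MT).
- The list is made by someone else: "A randomisation assignment sequence will be created by an independent member of the research team".
- The allocation is released in the PI's presence: "The results will be put into sealed opaque envelopes which the participants will open in their meeting with the PI". The PI is the one "who will explain the process to be followed depending on the group allocation", and so learns the arm of every participant in both groups.
- The neurologist is blinded to allocation. The PI is not blind to the MT group, and the PI's own blinding covers only the analysis of the end-of-study survey.

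The Intervention section adds: "The care as usual and MT group will be managed by the neurologist and receive MT from the PI". The Methodological considerations section confirms that there is a single manual therapist.

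The Data collection section says that the baseline questionnaire, HIT-6 included, may be completed on paper or online, at the first assessment or at home, as the participant chooses. Further on it says that completing it on paper at the first visit will be encouraged.

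**The concern.** One unblinded person makes the last contact before entry, obtains consent, attends the release of the allocation and then delivers the experimental treatment. A person in that position who has some idea of the next allocation can, without intending to, be more or less encouraging when seeking consent. Blinding the neurologist does not reach this step, because the neurologist's part in entry ends at screening. Recoding the data before analysis does not reach it either, because entry is settled by then.

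The second route is the baseline. The primary endpoint is the between-group difference in change in HIT-6 from baseline to 12 weeks. If the questionnaire goes home with a participant who has already opened her envelope, her baseline score may be coloured by relief or disappointment at her arm. Such a shift enters the primary contrast directly.

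The trial is open, has no sham arm and uses a patient-reported primary outcome. Secure allocation and an uncontaminated baseline are therefore among the few protections against bias that it can have.

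**Working it through.** **Order of steps.** Setting the sections side by side:

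| Step | Who | Where stated |
|---|---|---|
| Sequence created | Independent team member | Allocation |
| Screening | Neurologist or specialist nurse | Allocation |
| Information, risks and benefits, consent | PI | Allocation |
| Envelope opened | Participant, with the PI present | Allocation |
| Arm explained | PI | Allocation |
| Baseline HIT-6 | Participant, at the visit or at home | Data collection |
| MT delivered | PI, sole therapist | Intervention; Methodological considerations |

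The text puts consent before randomisation. It does not put the baseline HIT-6 before the opening of the envelope, and the home option allows the reverse order.

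**The plan's own figure.** The Sample size section gives a difference of 3.7, SD 4.91, power 80% and alpha 0.05 (two-sided assumed). The normal formula gives 2 × (4.91 × (1.960 + 0.842) / 3.7)² = 27.6 per group. The t-test version gives 28.6, so 29, as stated. Adding 10% gives 29 × 1.10 = 31.9, so 32. Thus 32 per group is a recruitment target with an attrition allowance: "Although this requires 29 participants in each group, 32 will be recruited to allow for attrition". It says nothing about how the sequence is restricted.

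**How well could the next allocation be guessed?** Suppose every earlier allocation is known and the guess is always the arm that is behind, with a coin toss when the arms are level. For a list, or a block, with m allocations to each arm in random order, the expected number of correct guesses is

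m + (2^(2m) / C(2m, m) − 1) / 2.

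- Unrestricted sequence: each guess is right with probability 0.5, so 32 of 64 (50%). No allocation is ever certain.
- One shuffled 32:32 list (m = 32): 2^64 / C(64, 32) = 10.07, so 32 + (10.07 − 1)/2 = 36.5 of 64 (57%). That is about 4.5 more than chance. The expected number of certain allocations at the end is 2 × 32/33 = 1.94.
- Blocks of 4, with the block size recognised (m = 2): 2 + (16/6 − 1)/2 = 2.83 of 4 (71%). Over 16 blocks this is 16 × 2.83 = 45.3 of 64, about 13 more than chance.

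Simulation of 10,000 sequences of each type gave 50.0%, 57.1% and 70.8%. The document states none of these sequence types, so all three are assumptions.

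**Effect on the primary contrast.** The comparison is (follow-up minus baseline) in the MT arm less the same quantity in the usual-care arm. If knowledge of allocation shifts mean baseline HIT-6 by d points in one arm, the contrast shifts by d in absolute value, to be set against the target of 3.7. The documents give no basis for a value of d.

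**The case against.** The case for leaving the procedure alone has real weight. The sequence is generated independently, the envelopes are sealed and opaque, and the participant opens her own. Screening is done before the PI meets her, by people who do not deliver MT, and the neurologist is blinded expressly to limit selection. Sealed opaque envelopes are an accepted method. The five-day option applies only when an immediate meeting cannot be held. With 64 participants over about seven months (64/7 ≈ 9 a month), there is little room to reorder patients. Most baseline questionnaires may well be completed at the first visit, since that is encouraged.

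This argument succeeds against several stronger readings that a reader might infer:

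- *Concealment is broken, or depends on the PI alone.* Being present at opening, after consent, does not in itself breach concealment, and the stated safeguards are genuine.
- *Totals are fixed at 32 per arm, so late allocations can be predicted.* The 32 is a recruitment target. No restriction of the sequence is stated, and an unrestricted one gives 50%.
- *Envelopes could be taken out of order.* This depends on custody and numbering, which a journal article may leave to the full protocol. The silence is not a fault here.
- *Selective entry could never be detected.* Baseline questionnaires and algometry are collected and each group is described, so marked selection could show as imbalance, though 64 participants give only a weak signal.
- *The PI has a personal stake through a doctorate.* The abstract says "The results will form part of a doctoral study" but not whose.

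What the argument does not remove is the stated combination of roles at the moment of release, or the freedom to complete baseline HIT-6 at home with nothing to place it before allocation.

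**Conclusion.** The point holds in limited form. The article states that the unblinded PI, who is the sole therapist, takes consent, attends the release of each allocation and learns it. It also permits a baseline HIT-6 completed after the arm is known. Both leave avoidable room for bias in an open trial with a patient-reported primary outcome. Neither shows that concealment fails or that bias will occur.

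The advantage from knowing earlier allocations ranges from none (50%) through about 57% to about 71%, according to an assumed sequence type. A correct guess does harm only if it is acted on. The size of any baseline effect cannot be derived from the document. That the PI accumulates knowledge of all earlier allocations is an inference from attending each opening and explaining each arm; it is not stated outright. This is a worthwhile low-cost improvement, not a defect that invalidates the design.

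**What to change.** Have the independent team member who creates the sequence also hold it. For each participant, the PI sends that member the participant number and confirmation that eligibility, signed consent and all baseline measures, HIT-6 included, are complete. The member logs the message with date and time and then returns the next allocation. From that moment the participant counts as randomised.

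If envelopes are kept as back-up, the same member holds them numbered in sequence, and the participant number is written on the envelope before it is opened.

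The home option for the baseline questionnaire can stay, provided that allocation waits until the questionnaire is returned. The Data collection section should say so.

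The cost is one message per participant, so 64 in all, to someone already assigned to randomisation. The allocation will involve a short wait, longer for participants who complete the baseline questionnaire at home.

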#### Intervention

The neurologist will manage the care as usual group alone. The care as usual and MT group will be managed by the neurologist and receive MT from the PI. The MT administered will consist solely of mobilisation, manipulation and soft tissue work. The PI will use a pragmatic approach to the MT administered, using any of the above manual interventions deemed clinically appropriate at each appointment based on assessment prior to treatment and participant feedback. The PI is an experienced chiropractor with over ten years’ clinical experience of chiropractic and soft tissue work, with postgraduate education and training in the management of CM. The treatment delivered will be recorded in the Case Report File (CRF). Failure to attend all manual therapy sessions will result in withdrawal from the study although provision will be made to provide an alternative appointment if the participant cannot make one as planned. Any change in a participant’s medical condition such that they fulfil the exclusion criteria above will result in their withdrawal from the study. Data from these participants would not be included in the final study results. Adverse events will be recorded in the CRF, and if classed as serious would be referred to the neurologist to be reported to the sponsor within 24 h of learning of the event and to the Main Regional Ethics Committee within 15 days in line with the required timeframe. The outline interventional procedure is shown in Table 3 with the project flow following the SPIRIT guidelines (Table 4).

**Table 3 Tab3:** Manual therapy protocol

1. Assess upper body^a^ posture in sitting	
2. Assess active and passive neck range of motion	
3. Assess shoulder girdle range of motion by raising each arm sideways from side of body up to ear	
4. Assess the temporomandibular joint	
5. Identify areas to treat in sitting position	
6. Administer MT using mobilisation, manipulation and soft tissue release in sitting position	
7. Assess patient shoulder girdle, neck and head supine and prone	
8. Administer MT in supine and prone position	
9. Following each session an outline of the MT used will be recorded.	
10. A total of 30 min will be allocated for each participant at these consultations	

^a^Upper body defined as from thoraco-lumbar junction upwards

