## Methods

### Study design

This will be a single centre, pragmatic Randomised Controlled Trial (RCT) involving 64 participants. The two groups will be “Tertiary care as usual” and “Tertiary care as usual plus MT”. The objective of the study is to measure the difference between the two treatment groups in CM. The study design adheres to the IHS and Consolidated Standards of Reporting Trials (CONSORT) guidelines [52, 53]. The study flow is outlined in Fig. 1.

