#### Data collection

All participants will be asked to complete a baseline questionnaire, comprising demographic information and the following validated instruments: Headache Impact Test (HIT6), the Migraine Specific Quality of Life Questionnaire (MSQ.V2),The perceived Stress Scale (PSS-10), State and Trait Anxiety Inventory (STAI-6),Brief Cope, Hospital Anxiety and Depression Scales (HADS) and the 12 Item Allodynia Symptom Checklist (ASC-12) The questionnaire will be available in paper or online format for completion at the initial assessment or at home at the discretion of the participant.

BMI values (from height and weight) will be calculated in the clinic and pain pressure thresholds will be taken using a somedic electronic pressure algometer [62] on each of the following muscles: Frontalis, Trapezius and Subocciptal. The order of these measurements will be taken randomly, which is an approach used in previous migraine studies [47, 48]. A distal site (forearm) will also be included to help provide a measure of wide spread central sensitisation [63]. These measures will be taken again at the end of the study after 12 weeks. Individuals assigned to the tertiary care as usual plus MT group will be given a 12 week treatment plan as recommended in IHS guidelines [52]. Sessions will be planned for Weeks 1, 2, 5, 8 and 12.The care as usual group will complete the normal 12 week cycle with the neurologist. Both groups will complete weekly diaries and an end of study questionnaire that duplicates the baseline questionnaire and includes a Patient Global Impression of Change Scale.

To encourage completion of data the participants will be encouraged to complete paper versions of the questionnaire at the first visit in the waiting area and leave it at reception, rather than taking home. Online versions will also be available. Reminder text message or emails will be sent out each week to encourage completion of the paper or online weekly diary.

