### Methodological considerations

The study is designed to be pragmatic and to balance the needs of efficacy and effectiveness in clinical research [67]. The HIT 6 score is used in this study as the primary outcome measure, as this is the only headache disability measurement tool with established validity in CM [54, 57]. The number of headache/migraine days will be collected as a secondary measure using a headache diary, a well established and valid measurement instrument [68–70] and recommended by the IHS.

Blinding and the placebo effects are potential limitations in this study. Although it is impossible to blind the PI for treatment, the final results will be re-coded to reduce the potential for analysis bias. The placebo effect is known to be high in all headache studies with acute treatment placebo being higher than prophylactic and tablets lower than injection [71, 72]. In studies of botox in chronic migraine, both in the immediate 12 week cycle and in longer term studies over multiple cycles, authors have cited placebo levels of between 20 and 49% [73, 74].

It is recognised that the MT group may experience a higher level of placebo as a result of the necessary interpersonal interactions [75, 76]. However in this study there is a high level of personal interaction with the headache nurse who applies the medical interventions and thus may be considered a balancing to interactions in the MT sessions.

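### Withdrawing participants who do not complete all manual therapy sessions, and dropping their data, removes people from one arm only after randomisation, with possible bias of unknown size and direction

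*Protocol article*

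**What the plan says.** Three consecutive sentences in the Intervention section of the protocol article matter here.

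- The attendance rule: "Failure to attend all manual therapy sessions will result in withdrawal from the study". The same sentence softens it: "provision will be made to provide an alternative appointment if the participant cannot make one as planned".
- A second, medical rule: "Any change in a participant’s medical condition such that they fulfil the exclusion criteria above will result in their withdrawal from the study".
- The consequence: "Data from these participants would not be included in the final study results".

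On who receives MT, the same section says "The neurologist will manage the care as usual group alone"; only the other arm also gets MT from the principal investigator. On the number of sessions, Data collection says "Sessions will be planned for Weeks 1, 2, 5, 8 and 12", which makes five.

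The Statistical analysis section names the tests (Student's t or Mann-Whitney for between-group differences) but no analysis set. Nothing elsewhere in the article keeps the data of withdrawn participants. The Background closes with the objective of determining the effectiveness of MT added to tertiary care, and Methodological considerations says "The study is designed to be pragmatic and to balance the needs of efficacy and effectiveness in clinical research".

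**The concern.** Attendance is observed only after randomisation and may depend on how the participant is doing. The Allocation section itself lists tenderness, aching and tiredness as possible reactions to MT, and a bad spell of migraine could keep someone from a session. Usual-care participants have no matching attendance condition, so a participant of the same kind stays in the results in one arm and leaves them in the other.

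The two groups then compared are not the two groups that were randomised. The difference in HIT-6 change mixes any effect of MT with the difference between people who do and do not complete five sessions. It also answers a narrower question than the stated objective: the outcome in completers, not the effect of offering MT on top of tertiary care. If withdrawal also ends follow-up, the week-12 data cannot be recovered afterwards by a better analysis.

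The medical-change rule also deletes data after randomisation. It applies to both arms, so it is a lesser problem, although the MT arm has five extra contacts at which such a change could be noticed.

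**Working it through.** **1. The plan's own figure.** Inputs from Sample size: difference 3.7, SD 4.91, α 0.05 (taken as two-sided), power 80%. For a two-sample t test, the noncentrality is 3.7 / (4.91 × √(2/n)). Power is 79.1% at n = 28 and 80.5% at n = 29, so the stated 29 per group reproduces. Recruiting 32 leaves room to lose 3 per arm (3/32 = 9.4%), in line with the 10% dropout in the Abstract. No stated number is wrong; the question is who is analysed.

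**2. Size of bias, simple form.** Let f be the fraction of the MT arm deleted and D the amount by which the deleted participants do worse than those kept. The mean of the kept group differs from the mean of the whole arm by

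bias = f × D.

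With D = 3.7 (an assumption): 3/32 × 3.7 = 0.35 points; 10/32 × 3.7 = 1.16 points, about a third of the target difference.

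**3. Size of bias, correlated attendance.** Assume a normal attendance tendency with correlation ρ to HIT-6 improvement, the k least adherent of 32 MT participants deleted, no true effect, and all 32 usual-care participants analysed. Then

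bias = ρ × 4.91 × m,

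where m is the expected mean of the 32 − k highest of 32 standard normal values: 0.176 for k = 3, 0.320 for k = 6, 0.501 for k = 10. For example, 0.5 × 4.91 × 0.176 = 0.43. The type I error (two-sided t test) was simulated; repeated runs agree to about 0.3 percentage points.

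| MT participants deleted | ρ = 0 | ρ = 0.3 | ρ = 0.5 |
|---|---|---|---|
| 3 of 32 | 0; 5% | 0.26; 5.5% | 0.43; 6.6% |
| 6 of 32 | 0; 5% | 0.47; 6.6% | 0.79; 9.8% |
| 10 of 32 | 0; 5% | 0.74; 8.5% | 1.23; 15.3% |

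Each cell gives the spurious HIT-6 benefit in points, then the type I error. A negative ρ (people stop because they feel better) gives the same sizes against MT: ρ = −0.3 with 3 deleted gives 0.26 points the other way.

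**4. How many might be removed.** The documents give no attendance rate. If each session is completed, after any rescheduling, with independent probability q, the expected loss is 32 × (1 − q⁵): 3.1 at q = 0.98, 7.2 at 0.95 and 13.1 at 0.90. If attendance is 95% and half of the misses are made up, q = 0.975, q⁵ = 0.881 and 28.2 of 32 are kept.

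**5. Power.** Against 32 usual-care participants, and with no bias, power is 82.4% with 29 MT participants, 80.1% with 26 and 76.1% with 22. Keeping all 64 with complete outcomes gives 84.3%.

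**The case against.** **Rescheduling.** A missed appointment can be replaced, so it would be wrong to infer that any single missed session removes a participant. This stands: the clause reduces the number affected, perhaps to about the planned 10%. It does not remove the rule. It also supports reading the rule as any session not made up, since a replacement for one appointment would be pointless if only those attending none were withdrawn.

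**Reach of the data sentence.** It directly follows the medical-change rule and could be meant for that group alone. This is possible. But the sentence closes a run of two withdrawal rules, and nothing says that non-attenders' data are kept. Even on the narrow reading, withdrawal from the study could end week-12 collection for these participants, again in one arm only.

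**Direction.** A reader might infer that the comparison is biased towards MT. The documents do not establish this, because they do not say why people would miss sessions. It is plausible, and no more.

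**Power.** A reader might also infer that the rule breaks the sample size. Independence between sessions is pessimistic, because misses tend to cluster in the same people, and the rate after rescheduling is unknown. A shortfall is possible but not shown. The 10% allowance must, however, also cover ordinary dropout.

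**Design claims.** The article says that it balances efficacy with effectiveness, so the word pragmatic alone does not settle the matter. It also says "The study design adheres to the IHS and Consolidated Standards of Reporting Trials (CONSORT) guidelines", but the content of those guidelines is not in the article, and this point does not rely on them. It rests on the stated objective and on the randomised comparison.

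**Left to an analysis plan.** A separate plan could define the analysis set, but this is not an omission: the article already commits to leaving data out.

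**Conclusion.** The point holds as a one-arm, adherence-based exclusion after randomisation. It follows from what the article states, on the natural reading of the data sentence. Followed as written, the rule takes away the protection of randomisation for the primary endpoint and makes the result depend on an untestable assumption about the people removed.

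The size is unknown. At the planned loss of about 3 of 32 it is modest under the assumed correlations of 0.3 to 0.5: at most 0.43 points and a type I error of about 6.6%. At 10 of 32 it reaches 1.23 points, a third of the 3.7-point target, with a type I error of about 15%. Both the number deleted and the correlation are assumptions, since the documents give neither. Neither a definite bias in favour of MT nor a definite loss of power should be claimed.

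**What to change.** Separate missing or stopping MT sessions from leaving the study. Whether a participant goes on receiving MT remains a clinical matter; this change concerns follow-up and data only.

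- State that missed sessions do not end follow-up or remove data, and seek the week-12 questionnaire and the weekly diaries from every randomised participant.
- Make the primary analysis all randomised participants as allocated, with a stated missing-data method.
- Apply the same analysis principle to those withdrawn for a change in medical condition, using data already collected.
- Report the full-attendance subset only as a labelled supplementary analysis.

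Cost: an amendment and some extra follow-up effort. Questionnaires and diaries can already be completed online, but week-12 algometry needs a visit and may be missing in non-attenders. Including partial attenders may dilute the estimate slightly compared with completers, which is appropriate to the question of adding MT to usual care.
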